### Study Setting

Individual elements of the study will be conducted in all four districts. The cRCT and process evaluation will be conducted in Lalaua and Muecate districts in Nampula Province, Northeastern Mozambique (Figure 1). The chemoprevention efficacy cohort study will be conducted in communities within the catchment area of one health facility in Lalaua district. The resistance marker study will be conducted in all four districts. As part of the process evaluation, several key informant interviews may be conducted with stakeholders who are based in Maputo.

To identify suitable districts for SMC implementation, a suitability ranking was conducted in-country with oversight from the WHO for all provinces. Criteria included a variety of factors: (1) seasonality eligible for SMC (ie, 60% of rainfall concentrated into 4 months), (2) mortality (ie, areas of highest mortality in children younger than 5 years using HMIS data), (3) access to care (ie, highest ranking given to areas where access to care was lowest), and (4) treatment-seeking behavior (ie, highest ranking given to areas where treatment-seeking behavior was lowest). The average category score was used to determine a final ranking and identify the top 20 suitable districts for maximizing the impact of SMC. From the list of suitable districts, additional consideration was given based on the importance of implementing the intervention in an area where no other new interventions were taking place so that effects could be attributable to only the intervention under investigation. Districts in Nampula Province were selected, as no indoor residual spraying or new long-lasting insecticide-treated net distribution campaigns had been targeted to these areas, allowing for a more robust attribution of SMC impact on malaria. 

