### Sample Sizes

#### Cluster Randomized Controlled Trial

Clusters will be selected for the intervention arm at the community level in two districts. The study will be powered to have an 80% chance of detecting a significant reduction in RDT-confirmed malaria incidence at the 5% confidence level using a chi-square test comparing two independent proportions in a cluster randomized design. We are aiming to detect a significant reduction in malaria incidence from 0.2 to 0.12 clinical episodes per child per high-transmission season, corresponding to the SMC round. The clinical episodes should be of sufficient severity to present to a health facility, and the reduction in episodes should be equivalent to an odds ratio of 0.66, or a minimum effect size of 33%. This is based on the assumption that the efficacy of SP+AQ in Northern Mozambique, where the prevalence of resistance alleles in circulating parasites is high, is half of that found in studies in West African settings. To account for the cluster randomized design, we assumed an intracluster correlation for malaria outcomes within communities of 0.23, based on data from SMC coverage surveys conducted by the Malaria Consortium in 2020 [27] and 2021 [28]. A cluster size of 15 children per community was selected, and children in the intervention and control arms were recruited in a ratio of 1:1.5. This resulted in a total sample size of 2850 eligible children in 190 clusters: 1710 in 114 clusters in the control arm and 1140 in 76 clusters in the intervention arm. A total of 76 communities from a list of all communities will be selected as intervention districts using a simple random method. Then, 114 communities will be selected at random from among those remaining for inclusion in the control arm.

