### Recruitment and Data Collection

#### Cluster Randomized Controlled Trial

In the control arm in both districts, compounds will be randomly sampled by researchers using household lists from selected communities, with one eligible child recruited at random from each household. After caregivers provide consent, children will be recruited and a short baseline questionnaire will be administered to collect individual data on each child and to confirm their eligibility. In the intervention arm, a researcher will follow a pair of community distributors as they administer SMC. In addition to variables such as experiences of fever within the past month among selected children, data on a range of variables relating to the selected child, their caregiver, and their household will be collected as part of the survey. These variables will include the selected children’s age, sex, and use of mosquito nets as well as the caregivers’ and heads-of-household’s level of education, occupational position, literacy level, household size, wealth (using the Simple Poverty Scorecard), primary language, and migration status, among other variables. Data on these variables will be collected in order to include potential confounders in the analysis for the association between the receipt of SP+AQ and clinically significant malaria. Children will be given SP+AQ by community distributors via directly observed therapy; in addition, blood samples will be taken and subsequent hemoglobin concentration measured using a HemoCue system (HemoCue AB). Children recruited into the study presenting at clinics will be identified using unique identification numbers and barcodes, and data on clinic visits, including suspected malaria cases and results of RDTs, will be matched to baseline questionnaire data to build a database for analysis.

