### Data Analysis

#### Cluster Randomized Controlled Trial

First, the characteristics of the eligible children in the intervention and control arms will be described and tabulated; these analyses will use survey weights obtained using population estimates for each community cluster. Next, a chi-square test will be performed to determine whether there is a significant difference in the proportions of children in each arm experiencing at least one confirmed malaria case during the study period, and exact odds ratios will be calculated.

Random-effects Cox proportional hazards regression models will then be fitted to estimate the difference in risk of an RDT-confirmed malaria case over time of follow-up; results will be expressed as hazard ratios, and a percentage effect size will be calculated. Model diagnostics will be run to verify the proportional hazards assumption, and random effects will be modeled at the community level to account for within-cluster correlation in malaria outcomes.

Two types of models will be fitted. The first will model risk of malaria based on time to first malaria case during each child’s first continuous period of follow-up; those experiencing an RDT-confirmed malaria case will be considered dropped from the sample, whereas those lost to follow-up will be considered right-censored. The second model type will account for recurrent events—using random effects for follow-up periods nested within individual children’s data—with children experiencing a malaria case considered to be “recovered” on the day of case confirmation and will continue to contribute follow-up information after this event.

Finally, to adjust for potential confounders, covariates based on data obtained from the baseline recruitment survey will be added sequentially to each of these two models by forward stepwise selection.

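### Forward stepwise selection, run separately in the two Cox models, makes the adjusted hazard ratios data-driven; one short pre-specified covariate set including district should replace it

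*Protocol article*

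**What the plan says.** The Data Analysis section for the cluster randomized trial sets three steps: a chi-square test with odds ratios; random-effects Cox models for first and for recurrent malaria cases; and last, an adjusted version of each, in which "covariates based on data obtained from the baseline recruitment survey will be added sequentially to each of these two models by forward stepwise selection". No entry criterion and no forced terms are given. The only structural term named is at community level: "random effects will be modeled at the community level to account for within-cluster correlation in malaria outcomes".

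Recruitment and Data Collection gives the purpose, "Data on these variables will be collected in order to include potential confounders in the analysis", and a list of child, caregiver and household variables that ends "primary language, and migration status, among other variables". District is not named in that list.

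On allocation, Study Setting states that "The cRCT and process evaluation will be conducted in Lalaua and Muecate districts". Sample Sizes states that "A total of 76 communities from a list of all communities will be selected as intervention districts using a simple random method", and that "114 communities will be selected at random from among those remaining for inclusion in the control arm". No district stratum is mentioned.

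**The concern.** In a randomised comparison the adjusted estimate should be defined before the outcomes are seen. Under stepwise selection the data choose the model, and the reported interval treats that model as if it had been fixed. Two separate selections can leave the first-event and recurrent-event hazard ratios adjusted for different variables, so a difference between them could not be put down to the event definition alone.

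The method also fits its stated purpose poorly. Selection driven by association with outcome (the usual form; the article does not state its criterion) can pass over a variable that differs between arms but is only weakly prognostic.

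That could matter here. Recruitment and Data Collection samples control children from household lists, whereas in the intervention arm a researcher accompanies the distributors during SMC delivery. The two routes could produce arms that differ by more than chance, and the adjusted models are the planned protection against that.

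**Working it through.** **1. The plan's own figure.** Inputs from Sample Sizes: proportions 0.12 and 0.20, ICC 0.23, 15 children per cluster, ratio 1:1.5, 5% level (two-sided assumed), 80% power.

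- Design effect = 1 + (15 − 1) × 0.23 = 4.22.
- Pooled mean = (0.12 + 1.5 × 0.20)/2.5 = 0.168.
- Intervention n = [1.96 × √(0.168 × 0.832 × (1 + 1/1.5)) + 0.842 × √(0.12 × 0.88 + 0.20 × 0.80/1.5)]² / 0.08² = 278, and control n = 1.5 × 278 = 417.
- Total = 695 × 4.22 = 2933, which is 2.9% above the stated 2850.
- Power at 1140 and 1710 children: 78.8% (pooled variance) or 81.4% (unpooled).

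The stated size is therefore reproduced closely. It rests on an unadjusted comparison of two proportions.

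**2. What stepwise selection does to the error rate.** The documents give no covariate effects, so this is a simulation under no treatment effect. From the plan: 76 and 114 clusters of 15, ICC 0.23. Baseline risk was set at 0.20, the plan's control proportion. Assumed: ten candidate covariates at cluster level, each with SD 0.5; entry at p < 0.05; linear regression of cluster proportions in place of the Cox models. Balanced scenarios used 8000 runs and shifted scenarios 5000. Entries are rejection rates at a nominal 5%.

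| Scenario | Unadjusted | All ten covariates fixed in advance | Stepwise |
|---|---|---|---|
| Balanced, no prognostic covariate | 4.9% | 4.7% | 5.1% |
| Balanced, three prognostic (log-odds 0.4 per unit) | 5.0% | 4.9% | 5.4% |
| Five weak factors (log-odds 0.2 per unit) shifted 0.2 SD between arms | 7.7% | 4.9% | 6.4% |
| The same five shifted 0.5 SD | 24.6% | 5.4% | 15.1% |

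For the stepwise column, simulation error (95%) is about ±0.5 points in the balanced rows and ±0.7 and ±1.0 points in the shifted rows. The balanced excess therefore cannot be told apart from 5%.

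Under a shift two things go wrong. Stepwise selection omits some weak but imbalanced factors and leaves about 58% of the unadjusted bias (0.0095 of 0.0163 at 0.2 SD; 0.0236 of 0.0403, or 59%, at 0.5 SD). The reported standard error is also too small: 0.0316 against an actual 0.0329 at 0.2 SD, and 0.0322 against 0.0371 at 0.5 SD.

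**3. What a district term could gain.** Let f be the share of between-community variance explained by district. The documents give no value. The design effect becomes 0.77 + 15 × 0.23 × (1 − f) = 0.77 + 3.45(1 − f).

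| f (assumed) | Design effect | Power, pooled |
|---|---|---|
| 0% | 4.22 | 78.8% |
| 5% | 4.05 | 80.5% |
| 10% | 3.88 | 82.3% |
| 20% | 3.53 | 85.7% |

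A cluster-level simulation gave a fall in standard error of about 0 to 2% for district risk differences of 0 to 0.10, and about 9% for a difference of 0.20.

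**The case against.** The strongest reply is that selection enters only at the last step. The trial is powered on two proportions ("The study will be powered to have an 80% chance of detecting a significant reduction in RDT-confirmed malaria incidence"), and the chi-square test and the unadjusted Cox models are fitted first. That stands. A reader might infer that the trial's confidence intervals are invalid in general; the documents do not support this, because only the adjusted models are affected.

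Next, the article is condensed. The entry criterion, forced terms and the final candidate list may be set out in an analysis plan that is not shown. That also stands for those details, but the choice of forward stepwise selection is stated outright and is not a gap. A reader might likewise infer that district is excluded from the models. The text neither names nor excludes it, and the list of variables is left open. Only the simple random draw is firm, and such a draw is valid without stratification.

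A reader might also treat chance imbalance between districts as bias. Suppose the 190 communities split 120 to 70 and district incidences were 0.15 and 0.30 (all assumed). The 95% range for intervention communities in Lalaua is then 42 to 54, and the risk ratio under no effect runs from 1.10 down to 0.91. The arithmetic is right, but this is random error with zero expected bias, built on inputs the documents do not give. Its SD is 3.27 × (1/76 + 1/114) × 0.15 = 0.011. The SE of the risk difference is √(0.2 × 0.8 × 4.22 × (1/1140 + 1/1710)) = 0.031. District would thus account for about 12% of the variance even on these assumptions.

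Nor can the district term be called free precision: step 3 shows that the gain may be nil. Last, the higher error rates in step 2 need a systematic difference between arms. The different recruitment routes make that plausible, but nothing shows that it occurred.

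**Conclusion.** The point holds for the adjusted models. They are to be chosen by the data, separately for each model and from an open list, and their nominal intervals ignore this. With balanced arms the effect on type I error is small (5.1 to 5.4% in simulation). With assumed shifts of 0.2 to 0.5 SD in five weak factors it is 6.4 to 15.1%, against 4.9 to 5.4% when all the shifted factors were fixed in the model in advance. Stepwise adjustment still did better than no adjustment in those cases (7.7% and 24.6%), so the case is for fixed adjustment and not against adjusting. These rates rest on assumed covariates, an assumed entry rule and a cluster-level linear model; they show direction and rough size only.

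A district term is advisable because two districts were sampled without a stated stratum. Its benefit runs from nothing to about 7 power points if district explains 0 to 20% of between-community variance.

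**What to change.** Before outcomes are examined, replace stepwise selection with one short covariate set used in both Cox models, for example district as a fixed effect, age, sex, net use and wealth score. Keep the community random effect, and keep stepwise selection as exploratory at most.

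Add fever in the past month only if it was recorded before the first SMC dose. The Abstract dates the cycles from December 2021, Study Design from January 2022, and data collection began in mid-January 2022. These dates must be reconciled before the variable can be treated as a baseline measure.

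Choose the set with the two recruitment routes in mind: a short list protects only against imbalance in what it contains. Stratifying the draw is no longer possible, since Results reports that data collection ended in mid-June 2022.

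The cost is wording. The survey variables are already in the baseline questionnaire and district follows from the community. The downside is that the list cannot be changed once the data have been seen.

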#### Chemoprevention Efficacy Cohort Study

Distributions and proportions of relevant mutations will be analyzed to compare the chemoprevention efficacy between groups of mutations. The blood drug concentrations will be analyzed as a cohort by mean, median, and SD, and statistical tests of their associations with treatment outcome—in particular, drug concentrations on day 7—will be performed. The focus will be on outliers with low levels of drug concentration based on the outcome measures described. Day-28 positivity will be associated with antimalarial drug resistance genotype.

#### Resistance Marker Study

Prevalence of *Pfdhps*, *Pfdhfr,*
*Pfcrt*, and *Pfmdr1* alleles in parasites obtained from participating children will be ascertained. Copy numbers of *Pfplm2* will also be quantified.

### Availability of Data and Materials

The associated study protocol and data collection tools will be made available upon request from the corresponding author. Quantitative data sets are available from the corresponding author upon reasonable request after the completion of primary analyses and results dissemination. Qualitative study data sets will not be available, as they may include identifiable information that could comprise participant confidentiality.

## Results

Data collection began in mid-January 2022 and concluded in mid-June 2022. Data analysis is expected to be completed by October 2022.

## Discussion

### Principal Findings

This hybrid research protocol will provide information about the feasibility, effectiveness, and chemoprevention efficacy of SMC using SP+AQ in Nampula, a northern province of Mozambique, where malaria transmission is high and seasonal.

The results from phase 1 of the Mozambique SMC implementation study demonstrated that SMC with SP+AQ is safe, feasible, and acceptable in the local context. The intervention was successfully delivered according to schedule and at the anticipated scale, achieving high coverage [28]. No serious adverse events were reported. Acceptability of the intervention among the population was high, with no negative rumors reported. The intervention appears to be highly effective: in a nonrandomized controlled trial, children who lived in a district where SMC had been implemented had 86% lower odds of developing clinical malaria during the peak transmission season compared with children who lived in the control district without SMC implementation [31]. There were high rates of sulfadoxine and pyrimethamine resistance, but one annual round of SMC does not appear to have had a negative impact on the resistance profile.

In phase 2 of the study, more work is needed to understand the efficacy of SP+AQ to clear existing infections and prevent new infections. This is what we mean by the term “chemoprevention efficacy.” The phase 2 chemoprevention cohort will determine whether SP and AQ in combination using current dosing regimens for SMC-eligible children are able to prevent infections over a 28- to 31-day period between cycles during the high-transmission season. Importantly, this cohort will also determine whether these drugs can also clear asymptomatic malaria to provide an estimate of chemoprevention efficacy in terms of prevention of both new and recrudescent infections. This will help determine the duration of effectiveness of SP+AQ. Further work is also crucially needed to map antimalarial drug resistance in these key populations in Mozambique, which has already been frequently highlighted in the literature [32]. The relationship between chemoprevention effectiveness and chemoprevention efficacy and how it relates to drug resistance is currently unclear. The chemoprevention efficacy component of this study aims to elucidate that relationship within the context of Northern Mozambique. The intention is to create a system where the relationship between these variables is better understood within and across malaria ecologies. We may find that drug resistance across Northern Mozambique and how it relates to effectiveness and efficacy covers a large geographical area, but this must be confirmed through future work once we better understand the dynamics of these interactions. Therefore, in the process of validating this methodology and analyzing these dynamics, it is prudent to create a geographical restriction to the assumptions of this protocol, whereby resistance to SP, in particular, may be representative of a given parasite population [13].

The study will also provide robust evidence of the effectiveness of SMC in an area outside of the Sahel in the form of a randomized controlled trial. This is the first time this work will have been done outside the Sahel and will prove crucial to national and global policy change. This study will support the extension of SMC outside Sahel geographies as already outlined by the WHO [33]. Work in close collaboration with key stakeholders, including the NMCP, the Mozambique Ministry of Health, and the Mozambique National Institute of Health, will ensure that clear and consistent recommendations will be provided in order to produce robust guidance for the national malaria control strategy. Findings will be presented at the province and district levels during meetings led by the research team and local stakeholders; these will involve community leaders, community distributors, and health professionals. Key messages will be provided to the audience, who will have the opportunity to give feedback regarding the development of new actions to secure continuity. Findings will also be presented during the next Mozambique Regional Scientific Days edition in 2023. Finally, results will be disseminated in peer-reviewed scientific journals and on the official Malaria Consortium website.

### Limitations

Administration of SP+AQ to ineligible children older than 59 months may raise concerns in relation to the development of drug resistance, as doses administered are unlikely to offer sufficient protection against malaria transmission. This also influences the secondary data analysis in the same way; administering SP+AQ to children older than 59 months could reduce the apparent effect size in the targeted age group.

## Abbreviations

AQ: amodiaquine
CNBS: Comité Nacional de Bioética para a Saùde
cRCT: cluster randomized controlled trial
DBS: dried blood spot
HMIS: health management information system
IPTi: intermittent preventive treatment in infants
NMCP: National Malaria Control Programme
*Pfcrt*: *Plasmodium falciparum* chloroquine resistance transporter gene
*Pfdhfr*: *Plasmodium falciparum* dihydrofolate reductase
*Pfdhps*: *Plasmodium falciparum* dihydropteorate synthetase
*Pfmdr1*: *Plasmodium falciparum* multidrug resistance gene 1
*Pfplm2*: *Plasmodium falciparum* plasmepsin 2
qPCR: quantitative polymerase chain reaction
RDT: rapid diagnostic test
SMC: seasonal malaria chemoprevention
SP: sulfadoxine-pyrimethamine
SP+AQ: sulfadoxine-pyrimethamine plus amodiaquine
WHO: World Health Organization
